## Abstract

**Abstract:**

Haemodialysis is a form of renal replacement therapy but is a catabolic process that not only filters toxins but is also known to lead to amino acid losses. Patients with chronic kidney disease often have a poor appetite and this in combination with limited dietary intake and the detrimental effects of haemodialysis can lead to the development of malnutrition. Between 20% and 50% of haemodialysis patients are thought to be malnourished. Malnutrition can worsen clinical outcomes and increase the risk of hospitalisation. We hypothesise that a nutritional supplement taken during haemodialysis may help to improve nutritional status.

The aim of this study is to conduct a pilot randomised controlled trial to assess the use of an intradialytic nutritional supplement on nutritional status. The objectives are to assess the feasibility of the trial including: recruitment and retention of participants; preference of nutritional supplements; compliance with the intervention; ease of completion of the questionnaires and appropriateness of the tools used. Secondary outcomes include clinical outcomes to obtain variance in the patient population and estimates of effect size to inform the sample size for a future definitive trial.

The trial is a single centre, randomised, parallel-group, two armed external pilot with an intervention and control group. The intervention group will take a nutritional supplement each dialysis session from a choice of prescribable drink or pudding style supplements. The control group will receive standard care.

Recruitment and feasibility elements are the primary outcomes. Recruitment will be to time (*t* = 6 weeks). In order to collect sufficient data to inform a future sample size calculation, we will aim to recruit 30 participants to obtain 12 evaluable per arm anticipating some drop out. Secondary outcome measures include clinical variables; hand grip strength, quality of life, weight and biochemistry completed at baseline, 1 and 2 months.

Descriptive statistics will be used to analyse the baseline characteristics of the recruited participants. Means, confidence intervals and standard deviations will be reported for the outcome measures of handgrip strength, dietary intake, quality of life and weight.

**Trial registration:**

ISRCTN37431579.

## Background

Malnutrition can be described as a nutrient intake lower than the nutritional needs of the individual (Fouque et al. 2008a). The presence of malnutrition is reported in approximately 20 - 50% of the haemodialysis population (Kopple 1997; Marcen et al. 1997; Aparicio et al. 1999) and is a factor in protein and energy wasting (PEW). PEW can be defined as '’…a depletion of protein mass and / or energy fuel supplies…..” (Fouque et al. 2008a) and has many associated consequences including increased mortality and morbidity, decreased quality of life (QOL) and increased risk of hospitalisation. There are many causes of malnutrition in the haemodialysis population including a decreased appetite and subsequent oral intake due to uraemic toxins (Carrero et al. 2008), protein losses on dialysis (Wolfson et al. 1982) and the catabolic effect of dialysis (Kalantar-Zadeh et al. 2003; Ikizler 2007).

Interventions to improve nutritional status through an increase in nutrient intake include the encouragement of food fortification techniques through dietary counselling with a renal dietitian (Akpele and Bailey 2004; Fouque et al. 2007), the use of oral nutritional supplements (ONS) and enteral or parenteral nutrition (Stratton et al. 2005) all of which have been shown to improve markers of nutritional status in some way.

The measurement of nutritional status is particularly difficult due to its complex causes and multiple variables. Nutritional status cannot be measured with a single parameter but should be classified using a variety of reproducible measures that predict outcome (Fouque et al. 2007). In view of this, previous studies measuring the impact of ONS in haemodialysis patients have used a variety of measures including albumin (Sharma et al. 2002; Kalantar-Zadeh et al. 2005) subjective global assessment (Fouque et al. 2008b; Calegari et al. 2011), QOL (Scott et al. 2009; Calegari et al. 2011) and anthropometric measures such as tricep skinfold thickness, mid arm muscle circumference (Beutler et al. 1997) and handgrip strength (Leal et al. 2011).

### Rationale for pilot study

Many of the previous studies aiming to improve nutritional status in this population recommend the need for further research as the most appropriate type of nutritional support, the timing of ingestion and which nutritional markers should be used to best assess their efficacy are still not clear. Larger scale trials have not been conducted to date and there are a number of parameters which need investigation before a definitive protocol can be developed.

### Aim and objectives

The aim of this study is to conduct a randomised controlled external pilot trial to assess the effect of an intradialytic oral nutritional supplement on nutritional status.

The primary objectives are to: demonstrate the feasibility, practicality, safety and acceptability of a nutritional intervention study protocol, including the willingness to be randomised to treatment, in the haemodialysis population; To determine recruitment, withdrawal and drop-out rates and use these to estimate such parameters over the longer term; To identify any preference for types of nutritional supplement and adherence to the intervention schedule; To determine the completion rates of the study questionnaires; To assess QOL, exploring whether the frequency and length of the QOL assessment is acceptable to this patient population.

Secondary outcomes include clinical measures of weight, handgrip strength, biochemistry and QOL with the confounding factor of dietary intake also being assessed. These clinical parameters will be utilised to estimate the effect size and variability of outcome measures to inform the sample size calculation for a full trial.

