### Sample size

To the authors knowledge no large randomised trials investigating the efficacy of intradialytic ONS have been conducted to date. Sufficient data on estimates of the standard deviation of the proposed outcome measures in this population are not available to enable a sample size to be calculated. This pilot trial is designed to collect this data to inform the sample size for a larger definitive trial in the future.

In order to collect sufficient data to inform a future sample size calculation we need 12 evaluable participants per arm, a total of 24 (Julious 2005). The aim will therefore be to recruit 30 patients to take into account any withdrawal.

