### Trial treatment

All participants will continue to attend their usual haemodialysis sessions at a frequency of 3 times a week and may receive information from a renal dietitian as per standard treatment, regardless of group allocation. The intervention group will in addition, be requested to ingest 1 ONS per dialysis session over a 2 month intervention period. Participants will receive a choice of ONS; a drink or two styles of pudding in various flavours will be available, with the aim to improve adherence through choice. The supplements vary in their nutritional composition but will all provide between 200 and 300 Kcal and 10.5 – 12 g protein per dialysis session. The differences in composition are small but the specific supplements have been chosen due to the low fluid volume they provide, an important factor in an often fluid restricted population.

Participants will complete a short questionnaire each dialysis session regarding their general wellbeing, intradialytic oral intake and for those in the intervention arm information about the amount of supplement taken and any preferences for type of ONS.

Handgrip strength, measured by dynamometry, QOL measured using SF-12V2 (2012), Weight in kg, biochemical markers, and dietary intake will be measured at baseline, month 1 and at the end of the intervention (month 2).

These clinical endpoints will help determine the most appropriate outcome measures and timing of data collection points for a larger randomised controlled trial and inform the sample size calculation.

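### The pilot's estimated effect size is named as an input to the definitive trial's sample size, but 12 evaluable per arm was chosen to estimate an SD and gives a between-arm difference only to about ±0.85 SD

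*Protocol article*

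**What the plan says.** Two places in the protocol article name effect size as something the pilot will supply for planning the full trial. Aim and objectives says: "These clinical parameters will be utilised to estimate the effect size and variability of outcome measures to inform the sample size calculation". The Abstract lists, separately from variance, "estimates of effect size to inform the sample size for a future definitive trial".

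The Sample size section gives a narrower reason for the pilot's size, namely that no formal calculation was possible: "Sufficient data on estimates of the standard deviation of the proposed outcome measures in this population are not available to enable a sample size to" [...]. On that basis it states that "we need 12 evaluable participants per arm, a total of 24", and adds: "The aim will therefore be to recruit 30 patients to take into account any withdrawal". It gives no target difference, significance level or power.

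Trial treatment adds that "These clinical endpoints will help determine the most appropriate outcome measures and timing of data collection points" for the larger trial, and that they will also feed its sample size.

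The Analysis section plans descriptive reporting of the secondary outcomes, with means, confidence intervals, ranges and SDs. The article names no other source for the definitive trial's target difference and gives no caution about the precision of an effect estimated from 24 patients.

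**The concern.** An SD and a treatment effect need very different amounts of data. A pilot of 24 can give a usable, if rough, SD. It cannot give a usable effect. The article justifies its size by the first purpose and then assigns the same data to the second.

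The required sample size varies with one over the square of the assumed effect, so error in the effect is magnified. If the pilot effect is high by chance and is used for planning, the definitive trial is too small. If it is low or negative by chance, the trial becomes impossibly large or is not run. Informing the next sample size is the declared purpose of the clinical data here, so the inputs should be ones that the pilot can support.

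**Working it through.** **Inputs.** From Sample size: 12 evaluable per arm, 24 in total, 30 to be recruited. The 12 per arm implies equal arms. Assumed here because the article does not state them: two-sided 95% intervals; 90% power and two-sided 5% for the definitive trial; true effects of 0.3 and 0.5 SD, used only as an illustrative range.

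**The plan's own figure.** No withdrawal rate is stated. A rate of 20% reproduces the target: 24 / (1 − 0.20) = 30. The 12 per arm is a cited rule for estimating an SD and has no power inputs to recompute.

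**Precision of the SD (22 df).** The 95% limits are √(22/χ²) times the estimate, which gives 0.77 to 1.42. The one-sided 80% upper limit is 1.16 times the estimate. Sample size scales with SD², so planning at that upper limit inflates it by 1.16² ≈ 1.35. That is a manageable allowance.

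**Precision of the difference, in SD units.** The half-width is t(0.975, 2n − 2) × √(2/n).

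| Case | Calculation | Half-width |
|---|---|---|
| 12 per arm, unadjusted | 2.074 × √(2/12) = 2.074 × 0.408 | ±0.85 |
| 15 per arm (all 30 evaluable) | 2.048 × √(2/15) = 2.048 × 0.365 | ±0.75 |
| 12 per arm, baseline-adjusted, r = 0.3 | 2.080 × √((2/12)(1 − 0.09)) | ±0.81 |
| 12 per arm, baseline-adjusted, r = 0.5 | 2.080 × √((2/12)(1 − 0.25)) | ±0.74 |
| 12 per arm, baseline-adjusted, r = 0.7 | 2.080 × √((2/12)(1 − 0.49)) | ±0.61 |

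The correlations are assumptions. In the unadjusted case an observed effect of 0.5 SD has an interval of 0.5 ± 0.85, that is −0.35 to 1.35 SD.

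**Chance of a pilot showing no benefit.** This is Φ(−δ/0.408). For δ = 0.3 it is Φ(−0.73) ≈ 23%. For δ = 0.5 it is Φ(−1.22) ≈ 11%.

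**Definitive trial actually needed.** Per arm, 2 × ((1.96 + 1.28)/δ)², which gives 234 for δ = 0.3 and 85 for δ = 0.5.

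**If the definitive trial is sized on the observed effect d.** Its true power is Φ(3.24 × δ/d − 1.96). This falls below 80% when d exceeds δ × 3.24/2.80 = 1.157δ.

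- δ = 0.3: the threshold is 0.347. P(d > 0.347) ≈ 1 − Φ(0.047/0.408) ≈ 0.45. Dividing by the 0.77 of pilots with a positive estimate gives about 59%; simulation that also lets the SD vary gives 60%.
- δ = 0.5: the threshold is 0.579. P(d > 0.579) ≈ 1 − Φ(0.079/0.408) ≈ 0.42. Dividing by 0.89 gives about 48%; simulation gives 48%.

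In the same simulation, with δ = 0.5, the sample size derived from a positive pilot estimate has a 10th to 90th percentile range of 18 to about 858 per arm, against the 85 needed.

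**The case against.** To inform a calculation is weaker than to plug in a point estimate. The article does not say that the observed effect will be the sole planning value. Confidence intervals are planned, so the imprecision would be visible, and a later team must still justify its own sample size. A pilot difference with its interval can properly be used to see whether a target is plausible. The figures for power below 80% assume uncritical use of the estimate, and the true effects of 0.3 and 0.5 SD have no source in the article.

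Most of this stands as a limit on how serious the point is. It does not remove the point: effect size is named twice as an input, no other source for the target is offered, and the half-widths do not depend on any assumed true effect.

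A reader might also infer from Trial treatment that the outcome or visit showing the largest difference will be carried forward, which would add upward selection bias. The article does not support that. It says only that the endpoints will help determine measures and timing. The Abstract, Aim and objectives, Primary outcomes and Analysis sections point to other criteria: completion, acceptability, appropriateness of the tools and time taken. Any figure for the bias from choosing the best result would describe a rule that the article does not contain.

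**Conclusion.** The point holds for the stated use of effect size. The pilot was sized for an SD, and its between-arm difference is known only to about ±0.85 SD unadjusted, or between ±0.6 and ±0.8 SD under the more favourable assumptions above. That cannot distinguish no effect from a moderate one. The unadjusted figures assume a 95% level and 12 or 15 per arm; the adjusted ones also assume the baseline correlation. The consequences for the later trial are illustrations that depend on the assumed true effect and on sizing directly from the observed value.

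This should be fixed, but it is not critical. Recruitment, retention, adherence and the other feasibility outcomes are unaffected, as is the use of the pilot to estimate variability. It would go too far to conclude that the definitive trial will be mis-sized, because the article does not commit to using the estimate alone.

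**What to change.** - In the Abstract and in Aim and objectives, remove the observed effect size as an input to the definitive sample size.
- State instead that the target difference will come from a prespecified important difference, and that the pilot will supply the SD (with an allowance for its own uncertainty, for example an upper confidence limit), the correlation with baseline, and attrition. The value of the important difference need not be given in this article.
- State that the observed between-arm difference and its 95% confidence interval will be used only to check that the target remains plausible.
- As a minor clarification in Trial treatment, say that outcomes and visits for the larger trial will be chosen on the completion, acceptability and measurement criteria that the article already sets out, not on observed between-arm differences.

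The cost is wording only. No patients, visits or data are added, and the conduct of the pilot does not change.

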## Methods/design

NOURISH is a two-arm parallel group randomised controlled external pilot trial of ONS versus standard care in haemodialysis patients. The trial will be conducted in a single centre with an intervention and control group. Both groups will receive standard care, but the intervention group will additionally take an ONS each dialysis session from a choice of prescribable drink or pudding style supplements in various flavours.

### Participant selection and setting

Adult renal haemodialysis patients will be recruited from an NHS hospital dialysis unit in Sheffield, UK. Patients will be identified, screened for eligibility and asked if they agree to participate by a renal dietitian when they attend one of their thrice weekly dialysis sessions. Inclusion and exclusion criteria are listed in Table 1. We will collect basic unidentifiable details on all eligible patients to allow completion of a CONSORT flow diagram (Figure 1).

**Table 1 Tab1:** **Inclusion and exclusion criteria for study participants**

Inclusion criteria	Exclusion criteria
• Adult haemodialysis patients (≥18 years of age)	• Amputees
• Received dialysis for at least 6 months prior to study screening	• Significant oedema
• Receive haemodialysis at least 3 times per week at the main haemodialysis unit (not satellite centre)	• Non fluent English
• Body Mass Index ≤22 kg/m2	• Receiving nutritional supplementation prior to study commencing or within 1 month of commencement in the study
	• Participants with an allergy to any ingredients in the nutritional supplements
	• Persistent hyperkalaemia or hyperphosphataemia (defined as the last 3 months).

**Figure 1 Fig1:**
[figure not shown]
**CONSORT flowchart of trial.**

The inclusion criteria include a BMI ≤22 kg/m^2^ this was chosen as a BMI at the lower end of the normal range (18.5 -25 kg/m^2^) has been indicated as detrimental to haemodialysis patients (Fleischmann et al. 1999; Leavey et al. 2001).

Amputees and those with significant oedema or an unstable dry weight will be excluded from this pilot trial due to the inaccuracy of assessing the height and thus the BMI of amputees and the oedema / fluid overload of patients falsely elevating their weight and consequently their BMI.

### Sample size

To the authors knowledge no large randomised trials investigating the efficacy of intradialytic ONS have been conducted to date. Sufficient data on estimates of the standard deviation of the proposed outcome measures in this population are not available to enable a sample size to be calculated. This pilot trial is designed to collect this data to inform the sample size for a larger definitive trial in the future.

In order to collect sufficient data to inform a future sample size calculation we need 12 evaluable participants per arm, a total of 24 (Julious 2005). The aim will therefore be to recruit 30 patients to take into account any withdrawal.

### Trial treatment

All participants will continue to attend their usual haemodialysis sessions at a frequency of 3 times a week and may receive information from a renal dietitian as per standard treatment, regardless of group allocation. The intervention group will in addition, be requested to ingest 1 ONS per dialysis session over a 2 month intervention period. Participants will receive a choice of ONS; a drink or two styles of pudding in various flavours will be available, with the aim to improve adherence through choice. The supplements vary in their nutritional composition but will all provide between 200 and 300 Kcal and 10.5 – 12 g protein per dialysis session. The differences in composition are small but the specific supplements have been chosen due to the low fluid volume they provide, an important factor in an often fluid restricted population.

Participants will complete a short questionnaire each dialysis session regarding their general wellbeing, intradialytic oral intake and for those in the intervention arm information about the amount of supplement taken and any preferences for type of ONS.

Handgrip strength, measured by dynamometry, QOL measured using SF-12V2 (2012), Weight in kg, biochemical markers, and dietary intake will be measured at baseline, month 1 and at the end of the intervention (month 2).

These clinical endpoints will help determine the most appropriate outcome measures and timing of data collection points for a larger randomised controlled trial and inform the sample size calculation.

### Primary outcomes

This trial is designed to assess feasibility outcomes. The recruitment rate, calculated as the proportion of those screened who are subsequently consented into the trial within the specified recruitment period will be assessed. The practicalities of recruitment and the study protocol including barriers to recruitment, adherence to the intervention (including palatability and preference for types of ONS), withdrawal and loss to follow-up, the feasibility, acceptability and appropriateness of data collection methods and data completion rates will also be recorded.

### Analysis

Primary analysis will be intention to treat but per protocol analysis will also be performed if relevant. Logs of patients screened and approached to participate, will be kept along with the time taken to approach, request consent and to complete each assessment to inform possible recruitment rates for future larger studies.

Data from all randomised patients will be analysed including those that may have withdrawn from the treatment arm but allow their data to be used for analysis up to the point of withdrawal. Descriptive statistics will be used to analyse the baseline characteristics of the recruited participants. Means, confidence intervals, minimum and maximum along with standard deviations will be reported for the secondary outcome measures of handgrip strength, dietary intake, QOL, biochemistry and weight.

### Ethical approval and research governance

The trial has approval from the Leeds East National Research Ethics Service Committee, reference number 13/YH/0092. The trial will be conducted in compliance with the protocol, GCP and regulatory requirements. The trial is sponsored by the local NHS Trust (Sheffield Teaching Hospitals NHS Foundation Trust) and will be subject to the research and development department management and monitoring procedures.

## Discussion

### Randomisation and blinding

Once eligibility has been confirmed and consent acquired the participants will be randomly allocated to treatment group via a bespoke web-based randomisation system provided by a University of Sheffield subsidiary company, EpiGenesys. The randomisation system will only reveal the allocated treatment (ONS or standard care) after participants details have been recorded and the participant entered into the trial. To reduce the risk of random imbalances in the number allocated to each arm of the trial, randomisation will be stratified by gender and age of participant. Due to the small sample size of this pilot study it may be difficult to stratify the sample population but we think it is important to test the randomisation system fully prior to a larger trial so stratification will be incorporated.

Due to the nature of the intervention trial participants and staff will not be blinded to treatment allocation. We will consider whether it would be better to include a placebo ONS in the definitive trial, but one of the aims of the pilot is to assess palatability of different styles of ONS so it is not feasible to blind in the pilot. The outcome assessor performing the handgrip strength and dietary assessment is also not blinded in the pilot but this will be addressed for the definitive trial.

Any side effects or adverse events reported by the patient, observed by clinical staff or determined during case note review will be recorded. There is a small risk of gastrointestinal disturbances and hypotension following ingestion of the ONS. There is a small risk attached to the conduction of the handgrip assessment, it could cause bleeding from the arteriovenous fistula, and so will be conducted on the arm without vascular access, this will also be documented to aid analysis.

